iii) To calculate and compare (where relevant) the incidence of potentially avoidable serious early neonatal morbidity and perinatal mortality, overall, and 1) in women whose LMC is reported as being a midwife where there is no evidence of medical input, 2) in women whose LMC is reported as being a midwife where there is evidence of medical input and 3) in women whose LMC is a general practitioner or obstetrician.

Inclusion criteria

- Singleton pregnancy
- Delivered during a specified time period (likely to be 1^st^ January 2006 and 1^st^ January 2010, The final inclusion period will be based on DHB birthing numbers and required sample size)
- Birthed at one of six specified District Health Boards
- Equal to or greater than 37 weeks gestation
- No identified major fetal or neonatal congenital, chromosomal, or metabolic abnormalities.

The sample size has been determined based on power calculations using the rarest outcome in the study, intrapartum fetal death. Sample size has been calculated using the Fleiss method with continuity correction in OpenEpi. Outcome rates have been estimated based on the Dutch Perinatal Mortality Study. An adequately powered simple study requires a sample size of 48 878. However, we need to increase the sample size because we wish to adjust the results for several major confounders particularly maternal age, antenatal risk, ethnicity, deprivation and parity of the mother. Furthermore, we wish to perform some subgroup analysis. For these reasons, we plan to double the sample size.

Exposure

- Reference group

Women who are reported to have a midwife as Lead Maternity Carer at booking and at admission in labour and where there is no evidence of medical input.

- Comparison groups

Women who are reported to have a midwife as LMC with evidence of medical input. Women will be included in this group if they have had one or more secondary care consultations or if they have had any antenatal admissions to hospital.

- Women who have had a General Practitioner, private obstetrician, or secondary care team as their LMC.

Outcomes

- Antepartum stillbirth: Antepartum stillbirth rates will be calculated as the number of fetal deaths that occur before the onset of labour divided by the total number of births in our cohort.

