- Low birth weight: Where the birth weight was recorded as less than 2500 grams. This variable was included as a negative control outcome in order to determine whether adjustment for confounding for the main outcomes was likely to have been sufficient. This is on the assumption that model of care is unlikely to substantially affect birth weight directly, but similar confounders may affect the relation between low birth weight, model of care and the outcomes

Covariates

The study will collect a number of maternal variables that may be potential confounders or mediators. These include:

- Maternal age: 12-18 yrs; 19-25 yrs; 26-35 yrs; 36-40 yrs and 40+.
- Ethnicity: NZ European, Māori, Pacific Island, Asian, Other.
- Deprivation: NZ Dep quartiles.
- Parity before delivery: 0, 1, 2, 3, 4+.
- Gestation at delivery: 37/40-38/40; 39/40-40/40; 41/40; 42+ weeks.
- Location of delivery: Primary birthing unit, secondary or tertiary hospital.
- Mode of delivery: Normal vaginal delivery, instrumental delivery, caesarean section.
- Pre-existing diabetes and/or hypertension: yes, no.

Analysis

- We will first calculate incidence rates (and 95% confidence intervals) of all outcomes for all groups combined and then for each group separately.
- We will then develop logistic regression models to calculate odds ratios (and 95% confidence intervals) for each major outcome comparing women receiving shared compared with midwife only care. The models will include potentially confounding patient characteristics such as age, parity, ethnicity and presence of pre-existing conditions.

Available data

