1. COVARIATES

All covariate data will be collected from the MOH. The covariates listed above are routinely collected, after hospital discharge, as part of the National Minimum Dataset (NMDS).

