**APPENDIX 1: DIRECTED ACYCLIC GRAPH DEMONSTRATING RELATIONSHIPS BETWEEN EXPOSURES, COVARIATES, AND OUTCOMES.**

BIRTH WEIGHT

AGE, ETHNICITY, SEP, SMOKING, BMI, PARITY, TRIMESTER OF REGISTRATION, PRE-EXISTING CONDITIONS

MODEL OF MATERNITY CARE

PERINATAL MORTALITY AND MORBIDITY

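### Smoking, BMI and trimester of registration are in the SAP's causal diagram but not in its covariate list, model description or stated data source

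*SAP*

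**What the plan says.** The SAP describes its covariates in five places.

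- **Appendix 1**, titled "DIRECTED ACYCLIC GRAPH DEMONSTRATING RELATIONSHIPS BETWEEN EXPOSURES, COVARIATES, AND OUTCOMES", has one covariate block: "AGE, ETHNICITY, SEP, SMOKING, BMI, PARITY, TRIMESTER OF REGISTRATION, PRE-EXISTING CONDITIONS".
- **Covariates** opens with "The study will collect a number of maternal variables that may be potential confounders or mediators". It then gives categories for age, ethnicity, deprivation (NZ Dep), parity, gestation, location of delivery, mode of delivery, and pre-existing diabetes and/or hypertension.
- **Analysis** describes the logistic models: "The models will include potentially confounding patient characteristics such as age, parity, ethnicity and presence of pre-existing conditions".
- **The sample size paragraph** (under Inclusion criteria) partly justifies doubling the sample by the wish to "adjust the results for several major confounders particularly maternal age, antenatal risk, ethnicity, deprivation and parity of the mother".
- **Available data, Covariates** states "All covariate data will be collected from the MOH" and adds that the covariates already listed are routinely held in the National Minimum Dataset.

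The Outcomes section also includes low birth weight as a negative control outcome, to judge whether adjustment for confounding was sufficient.

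**The concern.** This is a non-randomised comparison of care models, so its validity rests largely on the adjustment set. The diagram is the plan's own statement of which variables matter, yet the operational sections leave out three of them. No section says that these three are unavailable, excluded on purpose, or to be handled by sensitivity analysis. If they are not requested when the data are extracted, they may be hard to recover later. The result would then rest on a narrower adjustment than the plan's own diagram implies. A loosely worded adjustment set also leaves the final choice open until results can be seen.

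**Working it through.** **Step 1: set comparison.** SEP is mapped to NZ Dep, and pre-existing conditions to pre-existing diabetes and/or hypertension.

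| Item | Appendix 1 | Covariates list | Analysis sentence | Sample size paragraph |
|---|---|---|---|---|
| Age | yes | yes | yes | yes |
| Ethnicity | yes | yes | yes | yes |
| Parity | yes | yes | yes | yes |
| SEP / deprivation | yes | yes | **no** | yes |
| Pre-existing conditions | yes | yes | yes | not by name (antenatal risk is named) |
| Smoking | yes | **no** | **no** | **no** |
| BMI | yes | **no** | **no** | **no** |
| Trimester of registration | yes | **no** | **no** | **no** |
| Gestation, location, mode of delivery | **no** | yes | no | no |

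Three of the eight diagram items appear in no operational list. Three listed covariates are absent from the diagram. Deprivation is in every place except the model sentence.

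**Step 2: possible size of the bias.** The plan gives no figure to reproduce here, and every epidemiological input below is an assumption. For an omitted binary confounder with risk ratio RR and prevalences p1 and p0 in the two care groups:

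bias factor = [1 + p1(RR − 1)] / [1 + p0(RR − 1)]

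- RR 2, 10% v 20%: 1.10/1.20 = 0.92
- RR 2, 20% v 10%: 1.20/1.10 = 1.09
- RR 1.5, 10% v 20%: 1.05/1.10 = 0.95
- RR 2, 30% v 15%: 1.30/1.15 = 1.13

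Over these inputs the factor runs from about 0.92 to 1.13, so the distortion can go either way.

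**Step 3: comparison with precision.** The SAP gives 48 878 births for the simple study and plans to double it: 2 × 48 878 = 97 756. Assume a 40/60 split, which gives about 39 102 and 58 654, and the same outcome risk p in both groups:

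SE(log OR) = √[1/(39 102·p(1−p)) + 1/(58 654·p(1−p))]; 95% CI factor = exp(1.96 × SE)

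| Assumed outcome risk | SE(log OR) | 95% CI factor |
|---|---|---|
| 3% | 0.038 | 1.08 |
| 5% | 0.030 | 1.06 |
| 0.1% | 0.21 | about 1.5 |

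A bias factor of 0.92 or 1.09 is comparable with the interval for a common outcome such as neonatal unit admission, if its risk is 3-5%. It is small beside the interval for a rare death outcome.

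**The case against.** Several points on the other side stand.

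- **The lists are open.** The Covariates list, the model sentence and the sample size paragraph all give their items as examples. A reader might infer that the plan rules out adjusting for the three, but it does not. What stands is that they have no name, categories or source in any operational section.
- **The diagram's arrows are not visible in the text at hand.** A reader might infer that Appendix 1 declares the three to be common causes of care model and outcome. Only the labels can be read, so the firm statement is that they share a block with the accepted confounders. The mismatch does not depend on the arrows.
- **The negative control is a real safeguard.** A reader might think that smoking's effect on birth weight spoils it. A negative control outcome is meant to share the suspected confounders, and that is how it can signal residual confounding. It cannot remove that confounding, and a warning could not be acted on by adjustment if the fields were never collected.
- **No over-adjustment is planned.** A reader might infer that location or mode of delivery will enter the models. The plan groups them under possible confounders or mediators, and its model sentence names only maternal characteristics. Their role is unstated, which is a lesser matter.
- **The size is illustrative.** The formula gives crude bias. Adjustment for age, parity, ethnicity and perhaps deprivation would absorb part of any smoking or BMI imbalance. The effects of the three variables could offset one another as well as add up.

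**Conclusion.** The point holds as an internal contradiction that bears on bias. The adjustment set is not fixed, and as listed it lacks three of the eight covariates in the SAP's own diagram. Deprivation, named elsewhere as a major confounder, is also missing from the model sentence. The set comparison needs no assumption beyond the two mappings stated. The size rests wholly on assumed prevalences, risk ratios, group split and outcome risks. On those, one omitted variable could shift an estimate by roughly 8-9% (up to 13% in the range tried), in either direction. That matters for the commoner morbidity outcomes and is minor against the sampling error for deaths. The documents do not show that the results would be biased in a known direction, nor that bias would exceed the interval for every outcome.

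**What to change.** 1. State one primary adjustment set that matches Appendix 1: age, ethnicity, NZ Dep, parity, pre-existing conditions, smoking, BMI and trimester of registration. Use the same set in the Covariates, Analysis and sample size text.
2. Give the three added variables categories, a data source and a missing-data rule. Request them from the Ministry of Health or, where held, in the District Health Board extract that supplies lead maternity carer data. The SAP does not show that either source holds them, so check this first.
3. If any of them cannot be obtained, mark it as unmeasured in the diagram and pre-specify a quantitative bias analysis with stated ranges for prevalence and strength of association.
4. State that gestation, location and mode of delivery stay out of the primary models and are used only descriptively or as possible mediators.

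The cost is a modest data request and some redrafting. The downside is missing values in the added fields, hence the missing-data rule.

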1. EXPOSURE

For classifying the exposure status LMC data will be collected from individual DHBs. This category is the only one not available from the MOH who only hold LMC data for around 70% of women.

It is difficult to know how robust/complete the DHB data is before accessing it. Generally it is entered by clinicians. The available categories are as follows:

- LMC data:

LMC at booking

LMC at admission in labour

Labour care provided by*

Delivered by

Labour and delivery assisted by

*The last three are not collected by all the DHBs.

- Data to classify ‘medical input’:

A woman will be classified as having medical input if she has had antenatal secondary care consultations. This data is held by the MOH and comes from the National Non- Admitted Patient Collection. We will analyse the number of secondary care consultations and the type of consultation. The following codes are relevant:

| W03002 | First obstetric consults |
| --- | --- |
| W03003 | Subsequent obstetric consults |
| W03005 | Amniocentesis |
| W03006 | Chorion villis sampling |
| W03007 | Rhesus Clinics - multidisciplinary clinics |
| W03008 | Maternity foetal medicine clinics - multidisciplinary clinics |
| W03009 | Foetal medicine / anomalies clinics - multidisciplinary clinics |

Some of these categories are more likely to be associated with greater obstetric input; number of consults is also relevant. For example a woman who has one consult recorded under amniocentesis and no further consults likely had a negative test and limited obstetric input in her care. Sub-category analysis will therefore be necessary.

The number of obstetric related hospital admissions within the pregnancy is also available from the NMDs. These data are not detailed and we will be making the assumption that if a patient has been admitted to hospital she will have had some level of secondary care input. Again number of admissions is relevant and sub-category analysis necessary.

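### Births from six DHBs are pooled without naming DHB as an adjustment or stratification variable, so between-DHB differences may confound the odds ratios for the common outcomes

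*SAP*

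**What the plan says.** Under Inclusion criteria, a woman qualifies if she "Birthed at one of six specified District Health Boards". The window is several years long and not yet fixed: "The final inclusion period will be based on DHB birthing numbers and required sample size".

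Adjustment is described in four places, and none names DHB:

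- The sample-size paragraph lists "several major confounders particularly maternal age, antenatal risk, ethnicity, deprivation and parity of the mother".
- The Covariates section lists maternal, pregnancy and delivery variables. The nearest to a site variable is "Location of delivery: Primary birthing unit, secondary or tertiary hospital", which is a level of facility and does not identify the DHB.
- The Analysis section says "The models will include potentially confounding patient characteristics such as age, parity, ethnicity and presence of pre-existing conditions". The odds ratios are "for each major outcome comparing women receiving shared compared with midwife only care".
- The diagram in Appendix 1 has no node for DHB.

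No stratification, clustering or random effect by DHB appears anywhere.

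On data sources, Available data (Exposure) says "For classifying the exposure status LMC data will be collected from individual DHBs", that clinicians generally enter these data, and that their completeness is hard to judge before access. Consultations and antenatal admissions, which define medical input, come from national collections, as do the covariates and outcomes.

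**The concern.** DHB confounds the comparison if it is related both to the care group in which a woman is recorded and to the chance that her baby is recorded with the outcome. Both links are plausible. On the exposure side, each DHB supplies its own lead-carer data, and access to secondary consultations may vary locally even though the file that counts them is national. On the outcome side, admission to a neonatal unit is a local decision, and asphyxia and hypoxia are identified by diagnosis codes.

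Adjustment for patient characteristics need not remove such differences. The SAP's own safeguard, low birth weight as a negative control, is unlikely to reveal them either: a lower threshold for unit admission or a different coding habit does not change a recorded birth weight. A reassuring negative control could therefore coexist with confounding by DHB.

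At stake is a difference between DHBs being read as an effect of the model of care. With nearly 98,000 births, the intervals for common outcomes are narrow enough for a modest bias to matter.

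**Working it through.** **Text check.** DHB is missing from all four places listed above. The lists are open-ended, but the model sentence is confined to characteristics of the patient, which DHB is not.

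**Sample size.** The SAP states 48,878, to be doubled: 2 × 48,878 = 97,756. The 48,878 cannot be reproduced, because event rates, power and allocation are not given. It is used here only to set the scale of random error.

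**Assumed inputs (none from the SAP).** Six DHBs of equal size, with odds ratio 1 within each. Shared-care shares s = 0.25, 0.30, 0.35, 0.45, 0.50, 0.60, so Σs = 2.45 and Σ(1−s) = 3.55. Admission rates r rise in equal steps from 3% to 5%, 3% to 6% or 2% to 6%. All 97,756 births are taken to fall into the two groups compared.

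**Pooled risks and odds ratio.** p₁ = Σsr / Σs for shared care, p₀ = Σ(1−s)r / Σ(1−s) for midwife-only care, and OR = [p₁/(1−p₁)] / [p₀/(1−p₀)].

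**Random error.** n₁ = 97,756 × 2.45/6 = 39,917 and n₀ = 57,839. SE(log OR) = √[1/(n₁p₁(1−p₁)) + 1/(n₀p₀(1−p₀))], and the 95% factor is exp(1.96 × SE).

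With shares and rates rising together:

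| Rates | p₁ | p₀ | OR | SE | 95% factor | Lower limit |
|---|---|---|---|---|---|---|
| 3–5% | 0.1029/2.45 = 0.0420 | 0.1371/3.55 = 0.0386 | 1.09 | 0.033 | 1.07 | 1.02 |
| 3–6% | 0.1176/2.45 = 0.0480 | 0.1524/3.55 = 0.0429 | 1.12 | 0.031 | 1.06 | 1.06 |
| 2–6% | 0.1078/2.45 = 0.0440 | 0.1322/3.55 = 0.0372 | 1.19 | 0.033 | 1.07 | 1.12 |

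Adjusting for or stratifying by DHB returns the odds ratio to 1.00, because it is 1 within each DHB by construction.

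**Dependence on alignment.** The table assumes that the DHBs with most shared care also have the highest admission rates. Keeping the same shares and rates but assigning the rates to DHBs in all 6! = 720 orders, and taking the bias as a factor in either direction:

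| Rates | Median factor | Largest factor | Orders beyond the 95% factor |
|---|---|---|---|
| 3–5% | 1.03 | 1.09 | 80/720 = 11% |
| 3–6% | 1.04 | 1.13 | 192/720 = 27% |
| 2–6% | 1.06 | 1.20 | 330/720 = 46% |

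Half of the orders give an odds ratio below 1. The largest factors come from fully opposed gradients, with odds ratios of 0.92, 0.89 and 0.84.

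**Rare outcomes.** At an assumed rate of 0.1%, 97,756 births give about 98 events. With equal groups, SE = √[2/(48,878 × 0.001 × 0.999)] = 0.202, and the 95% factor is 1.49. The biases above would be small beside that.

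**The case against.** The strongest reply is that the SAP offers little direct evidence of a problem, and much of that reply stands.

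- **The fields that vary.** A reader might infer from "The last three are not collected by all the DHBs" that the exposure is recorded differently across DHBs. It does not follow. Those fields describe who gave labour care, delivered and assisted. The reference group is defined by the lead carer at booking and at admission in labour, and neither field is flagged. What remains is that completeness is unknown.
- **The source of the exposure.** A reader might infer that the whole exposure comes from the DHBs. Only lead-carer status does. The medical-input data that separate shared from midwife-only care among women with a midwife are national. A national file does not, however, even out local differences in access or practice.
- **Size.** The aligned figures of 1.09, 1.12 and 1.19 are close to the worst case for the assumed shares and rates, and they are crude. The planned patient-level adjustment could absorb part of any DHB difference.
- **Open lists.** The covariate and model lists are open, and facility level is collected. But facility level is not DHB, and the Analysis section does not name it.
- **Year and repeat births.** A reader might extend the point to both. Year has no support beyond the multi-year window: four assumed years, with shares spanning 10 to 20 points and rate ratios of 1.1 to 1.5, give odds ratios of only 1.01 to 1.05. Repeat births to one mother probably change the standard errors little.

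These replies limit the claim to a possibility. They do not show that DHB is handled.

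**Conclusion.** The point stands as an omission: a six-DHB cohort is to be analysed without DHB being named for adjustment or stratification, so between-DHB differences may confound the odds ratios for common, practice-dependent outcomes. The stronger statement, that they do confound them, is not supported, because the SAP reports no difference between DHBs in care mix, recording or admission practice. Size and direction are unknown.

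Under the assumed shares and rates, the bias is a factor of about 1.03 to 1.06 at the median ordering and up to 1.09 to 1.20 when the gradients align in either direction, against a 95% factor of about 1.06 to 1.07. It is therefore usually below random error in the two milder scenarios, near it in the widest, and clearly above it when gradients align. If either the shares or the rates do not differ between DHBs, there is no bias. If fewer than 97,756 births enter the two-group contrast, random error is larger. For the rare deaths the issue is minor.

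**What to change.** For the common outcomes (neonatal-unit admission, low Apgar score, and coded asphyxia or hypoxia where events allow), prespecify DHB as a fixed effect with 5 degrees of freedom, or stratify by DHB. Show DHB-specific odds ratios for neonatal admission, and add DHB to the diagram in Appendix 1. If DHB is left out, the SAP should say why.

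For the death outcomes, extra terms may produce sparse cells or separation. Use a stratified or penalised model there, or give DHB adjustment as a sensitivity analysis. Birth year, and standard errors clustered on the mother if mothers can be linked, are optional.

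No new data are needed for the main change, since the inclusion criteria already require DHB to be known. The cost is a few model terms and slightly wider intervals. Adjustment for DHB will not correct misclassified carer status within a DHB, so completeness of the lead-carer field should be tabulated by DHB. The choice should be fixed before results are seen, because adding DHB later would be post hoc.

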1. COVARIATES

All covariate data will be collected from the MOH. The covariates listed above are routinely collected, after hospital discharge, as part of the National Minimum Dataset (NMDS).

1. OUTCOMES

Outcomes are also collected from the MOH’s NMDS. We may need to use the Perinatal Maternal Mortality Review Committee Data to ascertain antepartum vs. intrapartum stillbirth as MOH data may not be sufficiently detailed.

**APPENDIX 1: DIRECTED ACYCLIC GRAPH DEMONSTRATING RELATIONSHIPS BETWEEN EXPOSURES, COVARIATES, AND OUTCOMES.**

BIRTH WEIGHT

AGE, ETHNICITY, SEP, SMOKING, BMI, PARITY, TRIMESTER OF REGISTRATION, PRE-EXISTING CONDITIONS

MODEL OF MATERNITY CARE

PERINATAL MORTALITY AND MORBIDITY
